### 2.3. Sample Size

The sample size (*n* = 40) was calculated a priori for a mixed repeated-measures design with two groups (control vs. experimental) and two assessment time points (pre- and post-intervention). The calculation assumed a significance level of α = 0.05, a statistical power (1 − β) of 0.80, and an expected small-to-moderate effect size (f = 0.25), with an assumed within-participant correlation of 0.5 and a nonsphericity correction of ε = 1.0. Under these assumptions, a minimum of 34 participants was required, evenly distributed as 17 individuals per group. Considering the potential for participant attrition and to ensure an adequate sample for pre- and post-intervention analyses, an attrition rate of approximately 15–20% was anticipated. Therefore, a total of 40 older adults will be recruited, with 20 participants allocated to the experimental group and 20 to the control group. The flow of participants through each stage of the study will be presented using a adapted CONSORT flow diagram adapted for quasi-experimental studies (Figure 1).

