### 2.8. Statistical Analysis

Data analysis will be performed using IBM SPSS Statistics software, version 30.0. Prior to analysis, data cleaning and coding procedures will be conducted to verify the absence of errors, outliers, or missing values. All statistical analyses will be carried out using a significance level of *p* < 0.05 and a 95% confidence interval.

At an initial stage, a descriptive and exploratory analysis will be conducted to characterize the sample and examine the distribution of the study variables. Sociodemographic variables (including age, sex, educational level, and comorbidities) will be summarized using absolute and relative frequencies for categorical variables, and measures of central tendency and dispersion (mean, median, standard deviation, and interquartile range) for continuous variables. Normality will be assessed using the Shapiro–Wilk test. Based on distributional assumptions, between-group comparisons will be performed using the independent-samples *t*-test for normally distributed continuous variables, the Mann–Whitney U test for ordinal variables or continuous variables with non-normal distributions, and the chi-square test for nominal variables.

To evaluate the effects of the virtual reality intervention, a two-way repeated-measures ANOVA will be conducted to test group-by-time effects (group × time). The primary analysis will follow the intention-to-treat (ITT) principle. A minimum of 20 imputed datasets will be generated, and this number may be increased depending on the proportion of incomplete data. Effect sizes will be estimated using partial eta-squared (ηp^2^) and interpreted as small (0.01), medium (0.06), or large (0.14) [36].

To control for inflation of type I error across secondary endpoints, *p* values for the prespecified secondary outcome analyses will be adjusted using the Holm–Bonferroni sequential procedure. This method was selected because it appropriately controls the family-wise error rate in the presence of multiple comparisons while being less conservative than the traditional Bonferroni correction. The correction will be applied to the secondary outcomes FES-I, ABC, SPPB, and handgrip strength. For the primary outcome, unadjusted *p* values will be reported. For the secondary outcomes, both unadjusted and Holm-adjusted *p* values will be presented, together with effect sizes and 95% confidence intervals [37].

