To control for inflation of type I error across the secondary outcomes, the Holm–Bonferroni sequential correction procedure will be applied to FES-I, ABC, SPPB, and handgrip strength [38,39]. This method was selected because it appropriately controls the family-wise error rate in the presence of multiple comparisons while being less conservative than the traditional Bonferroni correction [38,39]. For the primary outcome, unadjusted *p* values will be reported, whereas for the secondary outcomes both unadjusted and adjusted *p* values will be presented. Regarding statistical power, because the sample size was determined primarily based on the primary outcome, the secondary outcomes will be considered supportive and exploratory. With a statistical power of 80%, the study is expected to be more sensitive to large effects, whereas small effects in the secondary outcomes may not be detectable. Therefore, these findings will be interpreted with caution.

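### Section 2.8 reads small, medium and large labels off raw partial eta-squared, which at 40 participants is biased upward, has no sign, and gives near-uninformative labels to non-significant results

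*Protocol article*

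**What the plan says.** Section 2.8 of the protocol article tests the intervention effect as follows: "a two-way repeated-measures ANOVA will be conducted to test group-by-time effects (group × time"). The effect-size rule comes in the same paragraph: "Effect sizes will be estimated using partial eta-squared (ηp^2^) and interpreted as small (0.01), medium (0.06), or large (0.14"). It names no bias correction, gives no label for values below 0.01, and does not tie a label to the p value or the confidence interval.

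Inference in the same section rests on p < 0.05 with 95% confidence intervals. The primary outcome gets an unadjusted p value. The secondary outcomes (FES-I, ABC, SPPB, handgrip) get unadjusted and Holm-adjusted p values alongside effect sizes and 95% intervals. On power, the section says that "the study is expected to be more sensitive to large effects, whereas small effects in the secondary outcomes may not be detectable", and it asks for caution in reading the secondary results.

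Section 2.3 gives the sample size: "a minimum of 34 participants was required, evenly distributed as 17 individuals per group", and then "a total of 40 older adults will be recruited, with 20 participants allocated to the experimental group and 20 to the control group".

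**The concern.** Partial eta-squared is a proportion of variance. It is never negative, so chance differences push it upward, and the smaller the sample the stronger the push. With 40 participants or fewer, the lowest mark (0.01) lies below what chance alone typically produces.

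The statistic also has no sign. Hypotheses H1 to H4 state a direction, and Section 2.7.6 gives the control group an active exercise programme, so a difference in favour of the control group is possible. It would carry the same label as an equal difference in favour of virtual reality.

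What is at stake is interpretation. Section 2.1 describes the aim as feasibility and preliminary effects, and Section 2.8 calls the secondary outcomes supportive and exploratory. In such a report a non-significant result may be described by its size label, and here that label says very little.

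**Working it through.** **Inputs.** From Section 2.3: 40 recruited, 20 per group; a minimum of 34; f = 0.25, within-participant correlation 0.5, ε = 1.0, α = 0.05, power 0.80; and "an attrition rate of approximately 15–20% was anticipated". From Section 2.8: the group-by-time test and the marks 0.01, 0.06 and 0.14. Attrition of 15% or 20% leaves 40 × 0.85 = 34 or 40 × 0.80 = 32.

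**1. The plan's own figure.** For the interaction with m = 2 time points, the noncentrality is λ = f² × N × m / (1 − ρ) = 0.0625 × N × 2 / 0.5 = 0.25N, with 1 and N − 2 degrees of freedom. Power is 0.781 at N = 32 and 0.807 at N = 34, so the stated minimum of 34 reproduces. This confirms that the planned test has 1 and N − 2 degrees of freedom.

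**2. Partial eta-squared with no effect.** For a 1-df effect, ηp² = F / (F + N − 2), so ηp² ≥ c is the same event as F ≥ c(N − 2) / (1 − c). With no effect, F follows F(1, N − 2) and the mean of ηp² is 1/(N − 1). At N = 40:

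- mark 0.01: F ≥ 0.01 × 38 / 0.99 = 0.384, probability 0.539
- mark 0.06: F ≥ 0.06 × 38 / 0.94 = 2.426, probability 0.128
- mark 0.14: F ≥ 0.14 × 38 / 0.86 = 6.186, probability 0.017

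A simulation of 200,000 null trials of 20 against 20 gave 0.539, 0.128 and 0.017.

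**3. Results by sample size.** The significance threshold is Fcrit / (Fcrit + N − 2); at N = 40 this is 4.098 / 42.098 = 0.097.

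| N | Null mean | Null median | P(≥ 0.01) | P(≥ 0.06) | P(≥ 0.14) | ηp² at p = 0.05 |
|---|---|---|---|---|---|---|
| 40 | 0.026 | 0.012 | 0.539 | 0.128 | 0.017 | 0.097 |
| 34 | 0.030 | 0.014 | 0.574 | 0.163 | 0.029 | 0.115 |
| 32 | 0.032 | 0.015 | 0.586 | 0.177 | 0.035 | 0.122 |

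Every value from 0.01 to 0.06, and every value from 0.06 up to 0.097 at N = 40, therefore belongs to a non-significant result. An observed 0.01 at N = 40 has p = 0.54 and a 95% interval from 0 to about 0.14, so it spans the whole scale of labels up to large.

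**4. Alternative measures, N = 40, no effect.**

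- Partial omega-squared = (F − 1) / (F − 1 + N). It reaches 0.01 when F ≥ 1 + 0.01 × 40 / 0.99 = 1.404, probability 0.243. It reaches 0.06 when F ≥ 1 + 0.06 × 40 / 0.94 = 3.553, probability 0.067.
- Hedges' g, with marks of 0.2 and 0.5 (conventional values, assumed here because Section 2.8 gives none for g). The correction factor is 1 − 3/(4 × 38 − 1) = 0.980. |g| ≥ 0.2 means |t| ≥ (0.2 / 0.980) × √(20/2) = 0.645, probability about 0.52. |g| ≥ 0.5 means |t| ≥ 1.613, probability 0.115. These are close to the rates for raw partial eta-squared, so a change to g alone would not cure the labelling.

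**The case against.** A reader might infer that absent effects will be reported as effects. The text does not support that. The labels are descriptive and decide nothing: a null outcome is still declared significant 5% of the time, and a value of 0.01 would appear beside p = 0.54.

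A reader might also see a contradiction with the statement in Section 2.8 that small secondary effects may go undetected. There is none. A value in the small band is non-significant at this sample size, which agrees with that statement, and the section already asks for caution. That request, however, is made for the secondary outcomes and not for TUG.

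The marks are conventional benchmarks with no stated inequality, so the 54% and 13% depend on reading them as lower bounds. This stands. The upward bias does not depend on that reading, since both the null mean (0.026) and the null median (0.012) exceed 0.01.

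Sections 3.1 and 3.2 already give yardsticks in natural units, such as 2.3 s for individual TUG change and 1 point for SPPB. This softens the point, but Section 2.8 still names partial eta-squared as the effect size.

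Finally, much of the problem is sampling noise in a small study, as the Hedges' g figures show. That is why the interval, more than the choice of index, carries most of the remedy. That inflated values would enter later trial planning is possible but not stated: the article says only that its findings may inform future trials.

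**Conclusion.** The point holds as a limited weakness in reporting. At N = 40 raw partial eta-squared is biased upward and unsigned, and its labels hardly separate noise from a small effect. Read as lower bounds, the marks would label a true null small or larger in about 54% of analyses and medium or larger in about 13%. With 32 to 34 participants analysed, the rates rise to 57–59% and 16–18%.

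No test, error rate or sample size changes. The harm is confined to misleading size labels on non-significant results, TUG included.

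The rates assume normally distributed, independent change scores and complete data. Allocation is by pre-existing group (Section 2.2), so clustering could shift them, but the article gives no intracluster correlation with which to say by how much.

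**What to change.** In Section 2.8, state that the effect for each outcome is the signed between-group difference in pre-post change, in the outcome's own units (seconds for TUG, points or percentage for the scales, kg for grip), with its 95% confidence interval pooled over the imputed datasets. Name this for the primary outcome explicitly, since the sentence on that outcome mentions only p values.

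Drop the reading of small, medium and large from raw partial eta-squared. If a standardised variance-explained measure is wanted, use partial omega-squared with its interval, and require that any size label be read together with the interval.

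The cost is wording only. No further data or participants are needed, and the difference and its standard error come from the same comparison of change. The drawback is that reported effect sizes will look smaller.

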### 2.9. Complementary Analyses

To assess the feasibility of implementing the protocol within the primary health care setting, an analysis of feasibility indicators will be conducted using descriptive statistics and graphical representations:

#### 2.9.1. Recruitment Rate

The recruitment rate will be calculated as the percentage of individuals who agree to participate in the study relative to the total number of individuals invited. This indicator will allow the feasibility of the recruitment process and the effectiveness of the invitation strategies to be assessed. The target sample size (*n* = 40) was determined a priori for a mixed repeated-measures design with two groups (control vs. experimental).

#### 2.9.2. Retention Rate

The retention rate is defined as the percentage of participants who complete all planned sessions and assessments relative to the total number of individuals who initiate the study. This indicator will be used to evaluate participant retention and continuity throughout the protocol. Based on the planned sample size, a minimum retention rate of 80% is expected for both the experimental and control groups (*n* = 32).

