#### 2.7.4. Virtual Reality-Based Falls Prevention Workshop (Intervention) (Phase 2)

##### VR-Based Program Implementation Sessions

The intervention sessions corresponding to the Virtual Reality Program for Older Adults in Primary Health Care (PHC), aimed at falls prevention, will be implemented in accordance with the guidelines established in the Information Guide for Therapeutic Interventions with Immersive Virtual Reality (INVIRTUE) [33]. The clinical objective of the program is to reduce fall risk and maintain functional capacity within the framework of strategies for preventing functional decline in older adults. The intervention will have a total duration of twelve weeks, with a frequency of two sessions per week and an approximate duration of 60 min per session. The process will be supervised by an interdisciplinary team composed of occupational therapists and speech-language pathologists, who will provide continuous clinical monitoring, personalized feedback, and timely management of any adverse symptoms associated with the use of immersive virtual reality (iVR), such as dizziness, nausea, or disorientation.

Prior to the initiation of the program, an introductory session will be conducted to familiarize participants with the technology. During this session, explanatory audiovisual content will be presented, information regarding the therapeutic objectives will be provided, and a practical demonstration of device use will be performed. Participants’ questions will be addressed, and potential concerns related to the immersive experience will be discussed.

For the deployment of the intervention, appropriate preparation of the physical environment will be essential, ensuring a spacious, safe area free of obstacles. During each session, the instructor will activate the device and establish the necessary connection to project the experience onto an external screen, allowing the remaining group members to observe the activity and participate interactively through verbal feedback.

Subsequently, each participant will directly engage with the immersive virtual reality environments under constant supervision by the professional team, ensuring safety conditions, therapeutic support, and systematic monitoring of intervention tolerance.

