#### 2.9.4. Intervention Adherence

Intervention adherence is defined as the percentage of intervention sessions effectively completed by each participant relative to the total number of sessions planned in the protocol. This indicator will be used to assess the level of compliance and active participation of participants in the intervention. Based on the study design, a minimum adherence rate of 80% is expected in both the experimental and control groups (*n* = 32).

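### Retention is defined as full attendance at all 24 sessions plus assessments, so its 80% benchmark measures something much stricter than the attrition it mirrors and could misreport feasibility

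*Protocol article*

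**What the plan says.** Section 2.9.2 (Retention Rate): "The retention rate is defined as the percentage of participants who complete all planned sessions and assessments". The denominator is everyone who starts the study. The benchmark follows: "a minimum retention rate of 80% is expected for both the experimental and control groups", with n = 32 in brackets.

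Section 2.9.4 (Intervention Adherence) defines adherence as the "percentage of intervention sessions effectively completed by each participant relative to the total number of sessions planned". It then sets its own benchmark: "a minimum adherence rate of 80% is expected in both the experimental and control groups", again with n = 32 in brackets.

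Section 2.7.4 fixes the number of sessions: "total duration of twelve weeks, with a frequency of two sessions per week". Section 2.7.6 puts the conventional arm on the same schedule.

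Section 2.3 plans 40 participants (20 per group) from a minimum of 34, allowing for 15–20% attrition so that enough people remain for the pre- and post-intervention analyses. Section 2.9 says the feasibility indicators will be analysed with descriptive statistics and graphs.

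**The concern.** Retention normally tells the reader how many participants stayed in the study and supplied the outcome. Here one missed session out of 24 removes a person from the numerator, even if both assessments are complete. The indicator therefore combines two things that a feasibility study needs to keep apart: whether people stay to be measured, and whether they attend the programme.

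The benchmark does not fit the definition either. A figure of 80% is the complement of the 20% attrition in Section 2.3, which is loss from the pre/post comparison. Section 2.9.2 applies it to perfect attendance instead.

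Section 2.9.4 has a smaller flaw of the same kind. Adherence is a share of sessions computed within each person, yet its benchmark carries a count of people. It is left open whether the target is mean attendance of 80%, or 32 people each reaching some threshold.

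Feasibility is the declared aim, and retention and adherence are the only feasibility indicators with a percentage benchmark. As defined, neither reports how many participants provide the primary outcome. A study with little or no outcome loss could publish a low retention figure, and readers planning a later trial would take that figure as dropout.

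**Working it through.** **Inputs from the article.** 12 weeks × 2 sessions per week = 24 sessions in each arm (Sections 2.7.4 and 2.7.6; the familiarization session is not counted). Planned total 40. Benchmarks 80% for retention and 80% for adherence. Anticipated attrition 15–20%.

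**Step 1: reproduce the stated count.** 0.80 × 40 = 32, which matches Section 2.9.2. Attrition of 15–20% leaves 0.85 × 40 = 34 down to 0.80 × 40 = 32. The benchmark is thus the lower end of the Section 2.3 range.

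**Step 2: compare the tolerances.** Adherence of 80% is 0.80 × 24 = 19.2 sessions, so a person reaches it with 20 of 24 and may miss four. Retention allows no missed session.

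**Step 3: a case that needs no attendance model.** All 40 give both assessments and each misses one session. Retention as defined = 0/40 = 0%. Adherence = 23/24 = 95.8%. Loss of outcome data = 0%.

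**Step 4: independent absences (assumption).** The article gives no attendance rate, so a range is shown. With attendance probability p per session, P(all 24) = p^24:

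- p = 0.90: 8.0%, or 3.2 of 40
- p = 0.95: 29.2%, or 11.7 of 40
- p = 0.98: 61.6%, or 24.6 of 40
- p = 0.99: 78.6%, or 31.4 of 40

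An expected 80% requires p = 0.80^(1/24) = 0.991, which is 24 × (1 − 0.991) ≈ 0.2 missed sessions per person over 12 weeks.

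**Step 5: clustered absences (assumption).** Absence may instead concentrate in a few people. Let each person's attendance probability follow a beta distribution with mean μ and intraclass correlation ICC, so a = μ(1/ICC − 1) and b = (1 − μ)(1/ICC − 1). Then P(all 24) = B(a + 24, b)/B(a, b). The last column treats the 40 participants as independent of one another.

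| Mean attendance | Absence pattern | Complete all 24 | Attend at least 20 of 24 | P(at least 32 of 40 complete all 24) |
|---|---|---|---|---|
| 90% | independent | 8% | 91% | <0.001 |
| 90% | ICC 0.1 | 29% | 82% | <0.001 |
| 90% | ICC 0.3 | 53% | 81% | <0.001 |
| 90% | ICC 0.5 | 68% | 83% | 0.07 |
| 90% | ICC 0.8 | 83% | 87% | 0.75 |
| 95% | independent | 29% | 99% | <0.001 |
| 95% | ICC 0.1 | 54% | 93% | <0.001 |
| 95% | ICC 0.3 | 73% | 91% | 0.22 |
| 95% | ICC 0.5 | 83% | 92% | 0.75 |
| 95% | ICC 0.8 | 91% | 94% | 0.99 |

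The share attending at least 20 sessions stays between 81% and 99% throughout. The share completing all 24 runs from 8% to 91%, depending on how absences are distributed.

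**Step 6: can both targets be met?** If 80% of participants attend all 24 sessions, mean adherence is at least 0.80 × 100% = 80%, and at least 32 of 40 people also exceed an 80% personal threshold. Meeting the retention target therefore implies meeting the adherence target on either reading.

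**The case against.** The strongest reply is that little depends on this indicator. Section 2.9 makes the feasibility measures descriptive, the 80% figures are expectations, and no progression, stopping or failure rule is tied to them. Section 2.8 specifies an intention-to-treat primary analysis with at least 20 imputed datasets, so nobody leaves the TUG analysis for missing a session. Section 2.3 promises a participant flow diagram, which should show actual losses. All of this stands. A reader might infer that the study would be declared a failure despite complete outcome data, but the article contains no rule that would produce such a verdict.

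A reader might also infer that the two 80% targets contradict each other. They do not: Step 6 shows that they can be met together. They differ in tolerance, and the stricter one makes the other redundant.

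Finally, a reader who computes only p^24 might call the benchmark practically unreachable. That result rests on independent absences with a common probability, which the article does not state. Section 2.2 says the groups were chosen partly because their members attend regularly, and under strongly clustered absence 80% is attainable.

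It can also be said that conventional retention is computable from the planned data and that the bracketed count in Section 2.9.4 can be read as 32 people reaching 80%. Both are true. They show that the remedy is cheap, but Section 2.9.2 would still report a different quantity under the name of retention.

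**Conclusion.** The concern holds as a mis-specified feasibility indicator. Retention is merged with perfect attendance over 24 sessions, while its benchmark is borrowed from outcome attrition. The discrepancy can be as large as 0% reported retention with no outcome data lost, a result that needs no modelling assumption.

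How far the reported figure would fall in practice depends on attendance assumptions the article does not supply. Of the patterns tabulated, those with an expected 80% or more completing every session are the strongly clustered ones: ICC 0.8 at mean attendance 90%, and ICC 0.5 or above at 95%. Under independence about 99.1% attendance per session is needed. The target is demanding, not impossible.

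The consequence is a possible misreport of feasibility in a study whose stated aim is feasibility. No effect estimate, p value or power figure changes.

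**What to change.** - **Section 2.9.2:** define retention as the percentage of participants who start the study and complete the post-intervention TUG assessment, whatever their attendance. Keep 80% (32 of 40) as the benchmark for that quantity, which then corresponds to the attrition in Section 2.3.
- **Section 2.9.4:** report adherence per person as sessions attended divided by 24. State the benchmark as the proportion of participants attending at least 80% of sessions, that is at least 20 of 24, so that n = 32 is a count of people.
- **Optional:** report the proportion completing every session as a separate descriptive figure.

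The cost is two reworded definitions. Session counts per person and post-intervention TUG are already to be collected, so no new data are needed. The change should be made before results are known.
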